## AMENDMENTS

The following amendments and/or administrative changes have been made to this protocol since the implementation of the first approved version:

| Amendment number | Date of amendment | Protocol version number | Type of amendment | Summary of amendment                                                                                                                                                                                                                                                                                                                                                                                                                                                                                            |
|-------------------------|--------------------------|--------------------------------|--------------------------|------------------------------------------------------------------------------------------------------------------------------------------------------------------------------------------------------------------------------------------------------------------------------------------------------------------------------------------------------------------------------------------------------------------------------------------------------------------------------------------------------------------------|
| 1.                      | 25.5.2022                | 1.1                            | Amendment                | 1. Correction of differences between summary and eligibility section (sections 1. and 4.1)
2. Description of radiation exposure in LDCT, and risk-benefit ratio of LDCT(section 7.3)
3. Removal of incorrect wording related to another trial (section 11.2 and 12.4)
4. Correction of sample size calculations to detect 15% difference (75 vs 90%) between the study groups (section 1. and 17.2.1)                                                                                                         |
| 2.                      | 14.2.2023                | 1.2                            | Amendment                | 1. Offer a possibility for the study subjects randomized to standard-of-care smoking cessation to use the smoking cessation application after 6 months of follow-up.
2. Conversion of specificity of LDCT screening to a exploratory end-point
3. Introduction of two new secondary end-points
- Percentage of subjects who have reduced the amount of smoked cigarettes/d at 3 & 6 months after inclusion
- Magnitude and percentage of reduction in cigarettes consumed/d at 3 & 6 month after inclusion |

# 1. PROTOCOL SUMMARY

This is a randomized phase II trial investigating different smoking cessation methods in study subjects undergoing lung cancer screening with low-dose CT (LDCT). The study also evaluates feasibility and outcomes of LDCT screening and potential biomarkers and AI-based evaluation on CT-scans. The study subjects fulfilling I/E-criteria are randomized in 1:1 fashion to yearly LDCT for two rounds with standard smoking cessation (control) or same LDCT approach combined to mobile application based smoking cessation (intervention).

**Figure 1. Study flow-chart**

[figure not shown]

## Primary Objective

- To determine the efficiency of different smoking cessation methods

## Secondary Objectives

- To evaluate efficiency of different smoking cessation methods in reduction of smoking
- To assess the sensitivity, and positive predictive value of CT-screening
- To evaluate costs related to CT screening per patient per year

## Exploratory Objectives

- To evaluate specificity of CT-screening
- To evaluate lung cancer incidence (stage specific) and survival
- To evaluate the incidence of other important lung disease such as interstitial and fibrotic lung diseases, emphysema, bronchiectasis
- To collect the number of additional CT-scans, PET-CT scans, bronchoscopies, needle biopsies, and their results (positive vs. negative for cancer) initiated based on screening CT-findings
- To evaluate the percentage of subjects identified through newspaper advertisement and referral from primary care physician or occupational health physician
- To Evaluate Quality of life (QoL)
- To collect spectrum and grading of symptoms by electronic patient reported outcomes (ePRO)
- To evaluate correlation of ePRO symptoms to CT screen results
- To collect blood samples for potential biomarker analysis such as circulating tumor DNA (ctDNA)

- To evaluate artificial intelligence (AI)-based assessment of the LDCT scans

## Outcome Measures

### *Primary outcome measure(s)*

- The percentage of subjects who are actively smoking at 3 months after inclusion between the study arms
- The percentage of subjects who are actively smoking at 6 months after inclusion between the study arms

### *Secondary outcome measures*

- The percentage of subjects who have reduced the amount of smoked cigarettes/d at 3 and 6 months after inclusion between the study arms
- The magnitude and percentage of reduction in cigarettes consumed/d at 3 and 6 months after inclusion between the study arms
- Sensitivity, specificity and positive predictive value of CT-screening in the whole cohort
- Costs related to CT screening including additional investigations

### *Exploratory outcome measures*

- Specificity of CT-screening in the whole cohort
- Lung cancer incidence (stage specific) and survival
- Incidence of other clinically important lung disease in LDCT scans
- Number of additional CT-scans, PET-CT scans, bronchoscopies, needle biopsies, and their results (positive vs. negative for cancer) initiated based on screening CT-findings
- Percentage of subjects identified through newspaper advertisement and referral from primary care physician or occupational health physician
- Quality of life (QoL)
- Spectrum and grading of ePRO symptoms
- Correlation of ePRO symptoms to CT screen results
- Biomarker analysis of blood such as ctDNA
- AI-based evaluation of LDCT scans

### Trial Subject Population

The subjects at age of 50-74 with significant smoking history and current smoking status will be included in the study.

### Sample Size

A maximum of 200 subject will be included in the study.

### Eligibility

#### Inclusion Criteria:

1. Able to provide written informed consent
2. Age between 50-74
3. Smoked  $\geq 15$  cigarettes/day for  $\geq 25$  years or smoked  $\geq 10$  cigarettes/day for  $\geq 30$  years and are active smokers (smoking during the last two weeks)
4. Access to a smartphone (iPhone or Android)

#### Exclusion Criteria:

1. A moderate or bad self-reported health; e.g. unable to climb two flights of stairs
2. Body weight  $\geq 140$  kilogram
3. Current or past melanoma, lung, renal or breast cancer
4. A chest CT examination less than one year before inclusion
5. Has known psychiatric or substance abuse disorders that would interfere with cooperation with the requirements of the trial
6. Subject is unwilling or unable to comply with treatment and trial instructions
7. Any condition that study investigators consider an impediment to safe trial participation

### Trial Duration

The enrollment period is estimated to be 6 months. For each subject, the trial will consist of a screening (maximum of four weeks), and intervention period ( $\sim 1y \pm 3mo$ ). Survival and lung cancer data will be collected beyond the subject's active participation in the trial. The collection of the survival and lung cancer data of a subject is limited to 3 years from the inclusion.

### Statistical Methods

Eligible subjects are randomized (1:1) with stratification according to pack years ( $<30py$  or  $\geq 30py$ ), and age ( $<65$  or  $\geq 65v$ ) to smartphone based smoking cessation and control arm.

The study is powered (80%) with 155 subjects to detect 15% difference in (75 vs. 90%) in the number of active smokers at three and six months after inclusion with 90% confidence. With the expected dropout rate, the sample size is adjusted to 200.

### Intervention Schedule

The intervention period will initiate from randomization. At the randomization visit, all patients will be given written smoking cessation material and blood samples will be collected for biomarker analysis. The patients randomized to intervention arm will be given access to smartphone-based smoking cessation application with user training. The LDCT will be scheduled preferably within six weeks of randomization. After the LDCT, the patient will be informed of the results by mail. If no further procedures are required,

next LDCT will be scheduled for 1y +/- two months). With intermediate LDCT results, follow-up scan will be ordered at three months. With positive LDCT results, the patient will be referred to pulmonologist. At three and six months (+/- one month) after randomization, patient is called to evaluate whether they are active smokers and if they have quit, what is the date of smoking cessation. After the second round LDCT, the subject is scheduled a study visit in which LDCT results are communicated to the subject. In the case of negative LDCT results, patient enters survival follow-up. With intermediate results, new LDCT will be ordered at 2 or 12 months, and positive results will result in referral to pulmonologist. The survival follow-up period can last up to 3 years from inclusion.

### [Study Assessments](#)

The study assessments for the trial are shown in Table 1.

**Table 1. Schedule of Assessments**

|                                             | Screening (<4wks) | 0wks | 0-6wks                                  | T3mo (+/- 1mo) | T6mo (+/- 1mo) | T1y (+/- 2mo)                                                             | T3y (+/- 2mo)     |
|---------------------------------------------|-------------------|------|-----------------------------------------|----------------|----------------|---------------------------------------------------------------------------|-------------------|
| Informed consent                            | X                 |      |                                         |                |                |                                                                           |                   |
| Health information                          | X                 |      |                                         |                |                | X                                                                         | X                 |
| Smoking status                              | X                 |      |                                         | X              | X              | X                                                                         |                   |
| QoL assessment (EQ-5D, QLQ-C30+LC13)        |                   |      | X                                       |                |                | X                                                                         |                   |
| LDCT                                        |                   |      | X                                       |                |                | X                                                                         |                   |
| Blood sampling                  |                   |      | X                                       |                |                | X                                                                         |                   |
| Randomization                               |                   | X    |                                         |                |                |                                                                           |                   |
| Smoking cessation app (investigational arm) |                   | X    | X                                       | X              | X              |                                                                           |                   |
| Smoking cessation mat (control arm)         |                   | X    |                                         |                | X (optional)   | X (optional)                                                              |                   |
| Survival and lung cancer status             |                   |      |                                         |                |                | X                                                                         | X                 |
| CRF forms to be completed                   | HI                | Rand | LDCT 0
LDCT 0+
EQ-5D/QLQ
Bio 0 | Smo 3kk        | Smo 6kk        | HiFu 1v
Smo 1v
EQ-5D/QLQ
LDCT 1v
LDCT 1v+
Bio 1v
Sur 1v | HiFu 3v
Sur 3v |

Blood sampling for biomarker analysis (serum, plasma, and ctDNA)

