### 5.2 Screening

During the screening period, a subject's eligibility for the trial is determined by evaluation of the exclusion and inclusion criteria. Subjects will undergo a medical history review as part of the screening assessment.

The parameters listed below are collected and recorded into the CRF during the screening period. All procedures must occur within 4 weeks.

- Demographic data (age, race, and sex)
- Inclusion/Exclusion criteria
- Medical history and concomitant medications and interventional procedures
- Smoking history
- QoL with EQ-5D
- Blood sampling for biomarkers

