## 8. SCREENING RESULT COMMUNICATION TO THE SUBJECT

The results of screening will be communicated in writing to the participants. The letters of explanation will be issued withing four weeks of performance of the screening study.

The participants with positive finding will be directly referred to a pulmonologist.

The participants with intermediate findings will undergo another LDCT in a scheduled manner (Figure 3).

The letter will include:

1. Statement providing the overall results of the screening (negative, intermediate, or positive).
2. Statement providing further recommended steps on the screening results (timing of next LDCT, or referral)

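### The protocol gives conflicting times for the first quality-of-life and blood collection, and Table 1 lets the first quality-of-life measurement fall after allocation and up to six weeks of app use

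*Protocol*

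**What the plan says.** The protocol times the first quality-of-life and blood collection in three places.

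- **Section 5.2, Screening.** "The parameters listed below are collected and recorded into the CRF during the screening period", and "All procedures must occur within 4 weeks". The list includes EQ-5D as the only quality-of-life instrument, and "Blood sampling for biomarkers". Screening precedes randomisation.
- **Section 1, Intervention Schedule.** At the randomisation visit, "blood samples will be collected for biomarker analysis". Quality of life is not mentioned there. The same paragraph states that "The intervention period will initiate from randomization" and gives app-arm subjects access and training at that visit.
- **Section 1, Table 1.** The row "QoL assessment (EQ-5D, QLQ-C30+LC13" is empty at screening and at 0 weeks. It is marked at 0-6 weeks and at one year only. The blood row has the same pattern. Randomisation and app access are marked at 0 weeks. The form row of the table agrees: the 0-6 week column holds "LDCT 0 LDCT 0+ EQ-5D/QLQ Bio 0", after the randomisation form in the 0-week column.

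Section 7.4 times the first blood sample only as baseline, which does not settle the matter. On the scan, section 7.3 places the first LDCT within six weeks of randomisation, and section 8 adds: "The letters of explanation will be issued withing four weeks of performance of the screening study". Quality of life and biomarkers are listed as exploratory outcomes.

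**The concern.** A measurement that serves as a baseline in a randomised comparison should be taken before the subject knows the allocation. Subjects here necessarily know whether they were given an app. If Table 1 is followed, the first questionnaire may be answered with that knowledge, during a quit attempt supported by the app, or after a letter reporting the scan. Any of these can shift self-reported quality of life.

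Quality of life is scheduled only twice, so no other assessment can stand in for a first value that was taken late. For the QLQ-C30 and LC13 the problem does not depend on which section is followed, because section 5.2 omits them. At stake is any analysis that uses the first value as a baseline, by arm or in the whole cohort. For blood, the issue is simply that three sections give three times.

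**Working it through.** The protocol states no figure to reproduce here. The check compares the stated windows, with randomisation as week 0.

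**Inputs**
- Screening: at most 4 weeks, ending before week 0 (section 5.2, Table 1).
- Allocation, app access and written material: week 0 (Intervention Schedule, Table 1).
- First quality-of-life assessment: weeks 0 to 6 (Table 1), or weeks -4 to 0 for EQ-5D only (section 5.2).
- First LDCT: weeks 0 to 6 (section 7.3, Table 1).
- Result letter: no later than 4 weeks after the scan (section 8).
- App period: six months (section 10.1), taken as 26 weeks.

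**Exposure before the first questionnaire**
- Under section 5.2: none, for EQ-5D.
- Under Table 1, app arm: between 0 and 6 weeks of app use. At most 6/26 = 0.23, or 23% of the app period.
- Under Table 1, both arms: allocation can be known at any point in the window.

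**Scan result.** For a scan at week s, the letter is issued by week s + 4 at the latest. For s = 2 this is 2 + 4 = 6, so a scan at week 2 or earlier has its letter issued inside the 0-6 week window. A later scan may also be reported inside the window, because four weeks is an upper limit. Whether the questionnaire follows the letter depends on their order, which no section fixes. A questionnaire completed at or before the scan is free of the result.

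**Consequence for an analysis of change.** Let D(t) be the true difference between arms in mean quality of life at time t. Randomisation makes it zero in expectation before week 0. If the first value is taken at time t:

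- difference between arms in change = D(1 year) - D(t);
- bias relative to the one-year effect = -D(t).

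Adjusting for the first value as a covariate, with slope b, gives a bias of -b x D(t). Both vanish if the first value precedes allocation. For change in the whole cohort, the measured change omits whatever mean shift occurred between week 0 and t. A direct comparison of arms at one year estimates D(1 year) and does not use the first value.

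**Is it a reading artefact?** The assessment marks and the form row of Table 1 independently give the same column, so a shifted column is an unlikely explanation.

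**The case against.** The strongest reply is that the harm presupposes an analysis the protocol does not state. Quality of life is listed without a comparison between arms or a change from baseline, whereas the smoking outcomes are expressly compared between arms. The protocol never labels the first questionnaire a baseline, and a statistical analysis plan that is not shown may rely on the one-year value alone. This stands as a limit: the bias is conditional on how the data are used. It does not remove the contradiction, and no analysis can recover a questionnaire that was not collected before randomisation.

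Other parts of the reply also stand. The 0-6 week window includes week 0, so a late questionnaire is permitted but not required. The 23% is the extreme of that window and concerns the app arm only. Section 1 refers to Table 1 for the study assessments and the form row follows it, so sites may well act uniformly; mixed practice is possible but not shown.

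A reader might infer more than the documents support:

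- **That quality-of-life results will be biased.** They can be. D(t) is unknown and may be zero.
- **That the bias can be sized.** The protocol gives no information on how fast quality of life responds to quitting, app use or screening. Turning the exposure window into a percentage loss of effect would only restate whatever was assumed.
- **That the first questionnaire reflects the scan result.** This needs an early scan or a quick letter, together with a late questionnaire. It is the least certain part.
- **That blood must also precede randomisation.** Nothing in the documents shows that a draw up to six weeks later harms exploratory biomarker work. Sampling close to the LDCT is defensible.

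**Conclusion.** The inconsistency is real. EQ-5D has two conflicting times, blood has three, and the instrument list in section 5.2 is shorter than the one in Table 1. Followed as written, Table 1 allows the first of two quality-of-life measurements to come after known allocation, after up to 6 weeks (23%) of the app period in the app arm, and possibly after the result letter. Change-from-baseline and baseline-adjusted analyses can then be biased by an amount the documents do not allow one to estimate. This rests on two assumptions: that some questionnaires are completed after week 0, and that the first value is used as a baseline.

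A plain one-year comparison of arms is untouched by this point. So are the primary endpoints, which are smoking status at three and six months; Table 1 also records entry smoking status at screening. Because the outcomes concerned are exploratory, severity is low. The change is still worth making, because it is cheap and the missing measurement cannot be obtained afterwards.

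**What to change.** - In Table 1, move the first quality-of-life assessment (EQ-5D, QLQ-C30 and LC13) and its EQ-5D/QLQ form to the screening or 0-week column, and state that it is completed before randomisation.
- Give section 5.2 the same three instruments.
- For blood, choose one time point and state it identically in section 5.2, the Intervention Schedule, Table 1 (including the Bio 0 form) and section 7.4. It need not be before randomisation.

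The cost is a small written protocol amendment, with approval as section 15 requires, and moving forms in the CRF. Subjects already attend at screening and at randomisation, so there is no extra visit or procedure; the QLQ-C30 and LC13 are simply completed earlier. For subjects already enrolled, recording the date of the first questionnaire against randomisation, scan and result letter would show how many values were taken late.

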## ABBREVIATIONS

|           |                                                                          |
|-----------|--------------------------------------------------------------------------|
| AE        | Adverse event                                                            |
| CT        | Computer tomography                                                      |
| D         | Day                                                                      |
| DLT       | Dose limiting toxicity                                                   |
| ECOG      | Eastern Cooperative Oncology Group                                       |
| eCRF      | Electronic case report form                                              |
| EU        | European Union                                                           |
| IEC       | Independent Ethics Committee                                             |
| LDCT      | Low-dose computer tomography                                             |
| Mo        | Month                                                                    |
| NCI-CTCAE | National Cancer Institute-Common Terminology Criteria for Adverse Events |
| NSCLC     | Non-Small Cell Lung Cancer                                               |
| OS        | Overall survival                                                         |
| SAE       | Severe adverse event                                                     |
| SCLC      | Small Cell Lung Cancer                                                   |
| SOC       | Standard of care                                                         |
| SUSAR     | Suspected Unexpected Serious Adverse Reaction                            |
| Wk        | Week                                                                     |

